#### Other outcomes

Long-term (10-year) cognitive, behavioral, and motor developmental and general health outcomes of the participants and/or of their infants (among others with respectively WISC, ICBCL, movement-ABC, and pediatric check-up) are planned to be evaluated. For these plans, additional funding needs to be obtained. By then, ethical board approval will be obtained in a separate amendment. Permission to approach the participants and/or their children for follow-up research will be asked via the initial informed consent.

Furthermore, the residual material of the maternal blood samples after initial analyses is planned to be used for additional fundamental research on biomedical diagnostic tools such as placental markers, RNA-markers, methylation studies, (related) protein expressions studies for example longitudinal PlGF protein levels, or plasma RNA-markers (such as CSH1, GH1, ADAM12) and placental histological characteristics following the Amsterdam consensus criteria [24].

#### Participant timeline {13}

Participation takes 2 years from the moment of inclusion until the last follow-up. A schematic overview is shown in Fig. 1.

**Fig. 1 Fig1:**
[figure not shown]
Schematic overview

#### Sample size {14}

The primary outcome is a clinically relevant difference of 7 points on the Bayley-III scale [25]. With a standard deviation of 15 points in both treatment groups, an alpha of 0.05 and a desired power of 80% for a two-sample *t-*test, 74 patients need to be recruited in each arm of the nested RCT. Accounting for a 20% loss to follow-up of randomized fetuses, 185 women will be needed for the RCT in total. Assuming a 20% incidence of abnormal UCR within the cohort of SGA fetuses and accounting for an inclusion rate in the trial of 60% we calculate to need a cohort of 1542 patients. Despite the fact that we have a history of very low rates of loss to follow-up in our RCTs, we calculate 20% loss to follow-up of randomized fetuses because of the long interval (2 years) before assessment for the primary outcomes.

#### Recruitment {15}

Patients meeting the in- and exclusion criteria will be informed about the study primarily by treating physician and secondarily by the local research midwife/nurse. The patients will also be provided with written information about the study. Furthermore, an animation video can be shown or referred to with a QR-code, to support the oral and written information. Each eligible patient must be informed that participation in the study is voluntary and that withdrawal of consent will not affect her right to the most appropriate medical treatment or affect the doctor relationship.

### Assignment of interventions: allocation

#### Sequence generation {16a}

The allocation sequence is computer-generated using the online randomization service of Castor EDC (Castor Electronic Data Capture. 2019 [online] available at https://castoredc.com.). Randomization will be done using variable block sizes of 4 and 6, and will be stratified by gestational age (dichotomous; before or after 36 weeks) and participating hospital.

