**Methods:**

The DRIGITAT study is a national multicenter cohort study of women with singleton pregnancies between 32 and 37 weeks of gestation identified as SGA, with a nested randomized controlled trial (RCT) in case of an abnormal UCR (> 0.8). Recruiting centers are in The Netherlands. In the nested RCT, women are randomized to either immediate induction of labor or expectant management from 34 weeks in case of severely abnormal size (EFW or FAC < p3) and from 36 weeks in case of mildly abnormal size (EFW or FAC p3–p10). The primary outcome measure is the 7-point average difference in the composite cognitive score (CCS) and composite motor score (CMS) on the Bayley-3 at 2 years. Secondary outcome measures include a composite outcome of neonatal morbidity, perinatal mortality, mode of delivery, maternal quality of life, costs, and predictive value of serum biomarkers. Analyses will be by intention to treat. The required sample size is determined for the nested RCT as 185 patients.

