### Eligibility criteria {10}

In order to be eligible for inclusion in the observational cohort, a patient must meet all of the following criteria:Singleton pregnancyGestational age from 32 + 0 up to and 36 + 6 weeksIdentified SGA (estimated fetal weight (EFW) or fetal abdominal circumference (FAC) below the 10th percentile)

In order to be eligible to participate in the nested RCT, a patient must meet all of the above-described criteria and additional following criteria:Abnormal UCR of more than 0.8 (equals a CPR of less than 1.25) on at least 2 occasions with an interval of at least 1 workday (minimum of 15 h)

Two groups can be included in the RCT, dependent on FGR severity.EFW and/or FAC < p3 AND gestational age from 34 + 0 up to and including 36 + 6 weeks of gestationEFW and/or FAC < p10 AND gestational age from 36 + 0 up to and including 36 + 6 weeks of gestation

The EFW for inclusion or randomization should be calculated with the Hadlock 3 formula (including the FAC, head circumference (HC) and femur length (FL) [18], and the percentile value of the EFW should be based on the Hadlock reference curve [19].

The percentile value of the FAC should be based on the Verburg reference curve [20].

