#### Intervention description {11a}

Delivery from 34 weeks onwards when UCR is abnormal and fetal size is severely abnormal (EFW or FAC below p3), and delivery from 36 weeks when UCR is abnormal and fetal size is mildly abnormal (EFW or FAC p3–p10). Delivery has to be pursued as soon as possible from the moment of randomization.

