#### Implementation {16c}

Members of the local study teams are able to access the randomization service 24 h/day. After entering the needed variables (gestational age and treating center) the patient is randomized using Castor EDC.

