## Statistical methods

### Statistical methods for primary and secondary outcomes {20a}

Principal analyses will be performed on an intention-to-treat basis. The primary analysis will compare mean Bayley-III scores at 2 years and test the difference using a linear regression model controlling for the stratification factor. If women with suspected FGR (UCR > 0.8 or CPR < 1.25) allocated to the intervention group (timely delivery) have toddlers with better Bayley scores at 2 years, it will be concluded that timely delivery is beneficial based on UCR classification.

A sample of children born in the cohort will also be invited for Bailey-III testing and other outcomes assessed at 2 years of age. A sampling of patients from the cohort will be done against the index date of the trial patient.

Secondary endpoints will be analyzed as relative risks or differences in means with 95% confidence intervals. The chi-square tests and *t*-tests will be used for parametric dichotomous and continuous outcomes respectively. The Mann-Whitney tests with a median difference in medians (Hodges-Lehmann estimate) will be used for non-parametric continuous outcomes.

Data on pregnancy and short-term outcomes are expected only to be missing if patients withdraw consent. Long-term outcomes are anticipated to be missing in up to 15% of patients. The primary outcome will be assessed on a complete case analysis, with sensitivity analysis using multiple imputation.

An alpha of 0.05 is considered for statistical significance.

Data from the cohort study will be used as a comparator group to evaluate the course of all pregnancies, irrespective of UCR/CPR value, and inform whether different UCR/CPR thresholds or combination with other (serum) markers should be considered.

Statistical analyses will be conducted using the latest version of SPSS (SPSS Chicago, IL, USA).

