### Methods for additional analyses (e.g., subgroup analyses) {20b}

#### Biomarker analyses

There will be subgroup analysis and biomarker analysis to evaluate the effect of early delivery on the abovementioned outcome measures in subgroups defined by (a) an abnormal or normal serum level of placenta growth factor (PlGF), (b) gestational age categories, (c) other patient characteristics available at baseline such as gestational age and estimated fetal weight, and (d) the different components of UCR (MCA, UmbA). Given the chance of spurious findings with multiple testing in a limited sample size, these analyses will be primarily hypothesis-generating and significance will be determined after Bonferroni correction.

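### Size class defines the RCT entry groups but is in neither the randomisation nor the primary model, and the one-at-a-time age and size subgroups are partly confounded

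*Protocol article*

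**What the plan says.** Eligibility criteria {10} introduces the entry rule with "Two groups can be included in the RCT, dependent on FGR severity". Fetuses below p3 (EFW and/or FAC) may enter from 34+0 to 36+6, and fetuses below p10 only from 36+0 to 36+6. The Abstract gives the same scheme, "from 34 weeks in case of severely abnormal size (EFW or FAC < p3) and from 36 weeks in case of mildly abnormal size", and Intervention description {11a} repeats it for the milder group: "delivery from 36 weeks when UCR is abnormal and fetal size is mildly abnormal".

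Sequence generation {16a} says that randomisation "will be stratified by gestational age (dichotomous; before or after 36 weeks) and participating hospital". Implementation {16c} names the same two variables as those entered at randomisation: "After entering the needed variables (gestational age and treating center". For the primary analysis, section {20a} plans to "test the difference using a linear regression model controlling for the stratification factor"; it names no size term.

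The additional analyses {20b} list the subgroups as "b) gestational age categories, (c) other patient characteristics available at baseline such as gestational age and estimated fetal weight", alongside PlGF level and the components of the UCR. They are declared primarily hypothesis-generating, with a Bonferroni correction. Section {11b} lists, for the expectant arm, delivery from 38 weeks when EFW or FAC is below p10.

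**The concern.** The variable that separates the two entry groups is used for eligibility and then disappears. It varies only in the later gestational-age stratum, and nothing in the randomisation or the primary model accounts for it there.

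The consequence for the subgroups is more important. The group before 36 weeks contains only fetuses below p3, and the p3–p10 group contains only entries at 36+0 to 36+6. A contrast by age is therefore partly a contrast by size, and the reverse. The number of days by which expectant management can postpone delivery also changes with age at entry. If the treatment effect seemed to differ between listed subgroups, a reader could not say whether age, size or the length of the delay was responsible.

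**Working it through.** **1. The plan's own figure.** Inputs from Sample size {14}: difference 7, SD 15, alpha 0.05 (taken as two-sided), power 80%. A two-sample t-test needs 73.05 per arm, rounded up to 74 (power 80.5%). Then 2 × 74 = 148 and 148 / 0.80 = 185. Both stated figures reproduce. With 74 analysed per arm, the standard error of the treatment difference is 15 × √(2/74) = 2.47 points.

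**2. Cells that eligibility allows**, reading the stratification cut as 36+0, with the maximum delay counted to 38+0:

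| Size class | Entry 34+0 to 35+6 | Entry 36+0 to 36+6 |
|---|---|---|
| below p3 | eligible, 28 down to 15 days | eligible, 14 down to 8 days |
| p3–p10 | not eligible | eligible, 14 down to 8 days |

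One of four cells is empty. The delays are upper limits, because other criteria in {11b} can bring delivery forward.

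**3. Chance imbalance in the later stratum.** The document does not give the case mix, so these are assumptions: 148 analysed, a share f = 40–80% randomised at 36+0 or later, and a share q = 30–70% of those below p3.
- Children per arm in the stratum: n = 148f/2, about 30 to 59.
- SD of the between-arm difference in the share below p3: √(2q(1−q)/n). The largest value is √(0.5/29.6) = 0.13 and the smallest √(0.42/59.2) = 0.084, so 8 to 13 percentage points.
- Probability of a difference above 10 points: 24–44%; above 20 points: 2–12%.
- Shift in the overall treatment difference from a one-SD imbalance: f × SD × size effect. For an assumed size effect of 5 to 7 Bayley points, this runs from 0.4 × 0.119 × 5 = 0.24 to 0.8 × 0.092 × 7 = 0.51 points, against the 2.47 above.

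**4. Effect of omitting the covariate.** 5,000 simulated trials per setting: 148 children, 59 before and 89 from 36 weeks, half of the latter below p3, residual SD 15, blocks of 4 and 6 within age stratum, hospital not simulated. The estimate without the size term is unbiased, and type I error is about 5% with either model.

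| Assumed size effect (points) | Power, age only | Power, age and size |
|---|---|---|
| 5 | 80.5% | 80.6% |
| 7 | 78.4% | 79.6% |
| 10 | 78.6% | 81.2% |

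Simulation error is about √(0.8 × 0.2/5000) = 0.6 percentage points for a single figure.

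**5. How far the listed subgroups mix the two effects.**
- Before against from 36 weeks: the later group contains a share 1−q at p3–p10 and the earlier group none. The contrast carries 1−q, or 30–70%, of any treatment-by-size effect.
- Below p3 against p3–p10: all p3–p10 entries are late, but only a share fq/(1−f+fq) of those below p3 are. The contrast carries (1−f)/(1−f+fq) of any treatment-by-age effect, from 0.2/0.76 = 26% to 0.6/0.72 = 83%.

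**6. Can the effects be separated?** A model with treatment, age, size, treatment × age and treatment × size has full rank (6 of 6). Adding age × size and its interaction with treatment leaves rank 6 of 8, so only those joint terms are lost. The separated interactions have standard error 15 × √(4/n₁ + 4/n₂), where n₁ and n₂ are the total sizes of the two cells compared. At f = 0.6 and q = 0.5, age within the class below p3 gives 15 × √(4/59.2 + 4/44.4) = 6.0. Over the assumed range the standard errors run from 5.4 to 8.5 points. At 2.8 standard errors, only interactions of about 15 to 24 points would be detected with 80% power.

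**The case against.** The best defence is that nothing here threatens the primary conclusion. Randomisation balances size class in expectation, stratifying by age fixes it at below p3 before 36 weeks, and chance imbalance is sampling variation that the standard error already reflects. The subgroup list is open-ended, labelled hypothesis-generating and Bonferroni-corrected, and an analysis plan not shown could add a size covariate or joint subgroups. The separated contrasts are too imprecise to detect anything near 7 points.

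Most of this stands, and it rules out several stronger readings that a reader might infer:
- That severity is unprotected. It is not: the estimate is unbiased and type I error is held.
- That age and size effects cannot be separated, or are completely aliased. They can be separated within the class below p3 and within 36+0 to 36+6; the mixing is 26–83% under the assumptions, not 100%.
- That single-factor subgroups cannot inform the two delivery rules in the Budget impact analysis section. A size subgroup cut at p3 matches those rules approximately, apart from entries that qualify on FAC. What it cannot do is explain why the two would differ.
- That randomisation should be re-stratified. Stratifying within hospital on two age levels is defensible for 185 women, a third cell would thin the strata, and Trial status planned recruitment to end in the second half of 2023.

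The defence does not dispose of the rest. The protocol itself states the stratification factors, the model adjustment and the subgroup variables, so the point does not rest on silence. Calling a confounded contrast exploratory does not make it interpretable.

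**Conclusion.** The point holds as a modest one about precision and, mainly, interpretation. For the primary comparison the cost is small: a typical shift of 0.2 to 0.5 points, and a power gain from adjustment between nothing visible at a 5-point size effect and about 2.6 percentage points at 10. For the subgroups, each listed contrast carries a material part of the other effect, and the earlier and later entry groups have maximum delays that do not overlap. A difference between subgroups could not be credited to age or to size.

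All the sizes rest on assumed case mixes and size effects, because the document gives neither. The structural facts need no assumption beyond reading the stratification cut as 36+0: one empty cell, and no size term in the stated randomisation or primary model.

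**What to change.** Add size class at randomisation (below p3 against p3–p10, by the same EFW and/or FAC rule that eligibility uses) as a prespecified covariate in the primary regression of {20a}. In {20b}, replace the separate gestational-age and EFW contrasts with the treatment effect and its confidence interval in the three eligible cells: below p3 at 34+0 to 35+6, below p3 at 36+0 to 36+6, and p3–p10 at 36+0 to 36+6. Compare age only within the class below p3, and size only from 36+0. Keep all of this hypothesis-generating, and state that the age comparison still includes the difference in maximum delay.

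Size class is already recorded for eligibility, so no new data are needed. The sample size stays at 185, and neither the randomisation nor any clinical rule changes. The cost is one degree of freedom, and imprecise contrasts between cells (interaction standard errors of about 5 to 9 points under the assumed case mixes), which the report should say plainly.

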#### Concealment mechanism {16b}

The allocation sequence is computer-generated using Castor EDC (Castor Electronic Data Capture, Ciwit B.N.) and thereby unknown until the intervention is assigned.

#### Implementation {16c}

Members of the local study teams are able to access the randomization service 24 h/day. After entering the needed variables (gestational age and treating center) the patient is randomized using Castor EDC.

### Assignment of interventions: blinding

#### Who will be blinded {17a}

Due to the nature of the intervention, blinding of the intervention is not applicable. Outcome assessors and data analysts are blinded.

#### Procedure for unblinding if needed {17b}

Not applicable—the design is open label with only outcome assessors being blinded so unblinding will not occur.

### Data collection and management

#### Plans for assessment and collection of outcomes {18a}

Data collection forms can be found on www.zorgevaluatienederland.nl/DRIGITAT. Trained and authorized members of the local study team will collect and enter clinical trial data. Follow-up data is collected through online questionnaires with build-inn validation checks to minimize data entry errors. The neurodevelopmental (primary) outcome data is collected and assessed by a trained developmental psychologist. Trial data is assessed by the monitoring and quality assurance board of the NVOG consortium.

#### Plans to promote participant retention and complete follow-up {18b}

In collaboration with the “Patient Journey App” an application has been developed for DRIGITAT study candidates and participants to install on their phones. This application educates patients on topics concerning small for gestational age pregnancies, fetal growth restriction as well as the DRIGITAT study. The information in the app is adjusted and updated according to the personal situation of the patient (gestational age, candidate/participant). It aims to improve the participation rate and participant retention by providing information on a regular basis and sending reminders for questionnaires.

Participants can refuse the study intervention at any time for any reason if they wish to do so. Unless they refuse to allow further data collection, such participants will continue to be followed up and will be analyzed in the group to which they were originally allocated. Participants who decline follow-up will have no further trial data collected. Any results collected up to the point at which they decline follow-up will be analyzed.

When a woman is eligible for the RCT but is not willing to be randomized for the timing of the delivery, she remains—or can be included—in the observational cohort. Additionally, these patients will be asked to complete the same follow-up as the RCT participants, as mentioned in section 13.

#### Data management {19}

Data will be collected in a web-based registry (Castor EDC) by the NVOG Consortium clinical trials unit. The computer will randomly assign a unique numeric code for every participant that bears no relation to initials or date of birth. Data handling will be done with coded data, with the key (code to personal information linkage) only available to the local investigator and the research nurse working in the local center. Persons who have access to the data include investigators, research staff, monitoring and quality assurance personnel, and the data safety monitoring board (DSMB). Data will be preserved for the duration of 15 years as laid down by Dutch statute. The handling of personal data complies with the Dutch General Data Protection Regulation (AVG).

#### Confidentiality {27}

Personal data will only be available to the local study team, personal data will always be pseudonymized for the analyses. Anonymized trial data will be shared with other researchers—on request—to enable international prospective meta-analyses.

#### Plans for collection, laboratory evaluation, and storage of biological specimens for genetic or molecular analysis in this trial/future use {33}

Maternal blood samples (serum and plasma) are taken from all participants and stored for later biomarker analysis at the moment of inclusion. Blood sampling will be repeated once a cohort participant becomes an RCT participant and the previous sample was taken more than 2 weeks earlier. Biomarker analysis of these samples is performed centrally in batch after study closure. When consent is given (see “Additional consent provisions for collection and use of participant data and biological specimens {26b}” section), residual material of this blood is stored in a biobank for 50 years for future use.

## Statistical methods

### Statistical methods for primary and secondary outcomes {20a}

Principal analyses will be performed on an intention-to-treat basis. The primary analysis will compare mean Bayley-III scores at 2 years and test the difference using a linear regression model controlling for the stratification factor. If women with suspected FGR (UCR > 0.8 or CPR < 1.25) allocated to the intervention group (timely delivery) have toddlers with better Bayley scores at 2 years, it will be concluded that timely delivery is beneficial based on UCR classification.

A sample of children born in the cohort will also be invited for Bailey-III testing and other outcomes assessed at 2 years of age. A sampling of patients from the cohort will be done against the index date of the trial patient.

Secondary endpoints will be analyzed as relative risks or differences in means with 95% confidence intervals. The chi-square tests and *t*-tests will be used for parametric dichotomous and continuous outcomes respectively. The Mann-Whitney tests with a median difference in medians (Hodges-Lehmann estimate) will be used for non-parametric continuous outcomes.

Data on pregnancy and short-term outcomes are expected only to be missing if patients withdraw consent. Long-term outcomes are anticipated to be missing in up to 15% of patients. The primary outcome will be assessed on a complete case analysis, with sensitivity analysis using multiple imputation.

An alpha of 0.05 is considered for statistical significance.

Data from the cohort study will be used as a comparator group to evaluate the course of all pregnancies, irrespective of UCR/CPR value, and inform whether different UCR/CPR thresholds or combination with other (serum) markers should be considered.

Statistical analyses will be conducted using the latest version of SPSS (SPSS Chicago, IL, USA).

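### Randomisation uses two stratification factors, but the primary model names only one, unspecified, and the secondary tests use neither; the cost is modest and conservative, and the repair is a wording change

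*Protocol article*

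**What the plan says.** Under Sequence generation {16a}, randomisation uses variable blocks and "will be stratified by gestational age (dichotomous; before or after 36 weeks) and participating hospital". Implementation {16c} confirms two factors: "After entering the needed variables (gestational age and treating center) the patient is randomized using Castor EDC".

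Statistical methods {20a} then has the primary analysis of the Bayley-III score "test the difference using a linear regression model controlling for the stratification factor". The factor is singular and is not named.

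For the rest, "Secondary endpoints will be analyzed as relative risks or differences in means with 95% confidence intervals". The tests are specified: chi-square and t "tests will be used for parametric dichotomous and continuous outcomes respectively", and "The Mann-Whitney tests with a median difference in medians (Hodges-Lehmann estimate) will be used for non-parametric continuous outcomes". None of them uses the strata.

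Two other sections bear on whether the strata predict outcome. Background and rationale {6a} associates late prematurity with transitional neonatal disease and with poorer neurodevelopment. Operational or practical issues expects slight differences in management between hospitals that affect outcomes, and says guidelines are provided to counter this.

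**The concern.** Stratified blocks balance the arms within strata, so variation between strata largely drops out of the true sampling error of the treatment difference. An analysis that ignores the strata still counts that variation as noise. Its confidence interval is then too wide and its test rejects too rarely.

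Two things follow here. The primary model can be read as gestational age only, hospital only, or both, and these readings give different standard errors for the trial's main test. For the secondary outcomes there is no such doubt, because the named methods leave the strata out. Jaundice and hypoglycaemia, which the article ties to preterm delivery, are components of the perinatal morbidity composite tested in this way.

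**Working it through.** **Inputs from the article (Sample size {14}).** Difference 7 points; SD 15; alpha 0.05; power 80%; two-sample t-test; 74 per arm; 20% loss; 185 in total.

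**Assumed, not in the article.** Share of outcome variance explained by the strata (R²): 0 to 0.20. Number of hospitals: 10 or 25. Half of the women in each gestational-age stratum.

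**1. The plan's own figure.** Normal approximation: 2 × 15² × (1.960 + 0.842)² / 7² = 72.1, so 73 per arm. The exact two-sided t-test gives 73.05, rounded up to 74. Then 148 / 0.80 = 185. Both figures reproduce. Power at 74 per arm is 0.810 (normal) or 0.805 (t).

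**2. Wholly unadjusted analysis of a continuous outcome.**

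- Reported SE = 15 × √(2/74) = 2.466.
- True SE under stratified blocks ≈ 2.466 × √(1 − R²).
- True alpha = 2 × [1 − Φ(1.96 × reported SE / true SE)].
- Unadjusted power = Φ[(7 − 1.96 × reported SE) / true SE].
- Adjusted power = Φ[7 / true SE − 1.96], ignoring lost degrees of freedom.

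| R² | True SE | SE overstated by | True alpha | Power unadjusted | Power adjusted | Points lost |
|---|---|---|---|---|---|---|
| 0 | 2.466 | 0% | 0.050 | 0.810 | 0.810 | 0 |
| 0.05 | 2.404 | 2.6% | 0.044 | 0.816 | 0.830 | 1.4 |
| 0.10 | 2.339 | 5.4% | 0.039 | 0.823 | 0.849 | 2.6 |
| 0.20 | 2.206 | 11.8% | 0.028 | 0.837 | 0.888 | 5.1 |

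Example at R² = 0.10: (7 − 1.96 × 2.466) / 2.339 = 0.93, power 0.823; 7 / 2.339 − 1.96 = 1.03, power 0.849. The difference tested is 7/15 = 0.47 SD. The SE ratio and true alpha do not depend on the number of patients; the power figures do.

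**3. Readings of the primary model, by simulation.** 148 children, blocks of 4 and 6 within gestational age × hospital, hospital as fixed effects, 3000 runs per scenario (Monte Carlo error about 0.7 points: √(0.8 × 0.2 / 3000) = 0.007). Power for 7 points:

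| Hospitals | R² gestational age + hospital | No adjustment | Gestational age only | Both |
|---|---|---|---|---|
| 10 | 0.10 + 0.10 | 0.829 | 0.858 | 0.878 |
| 25 | 0.05 + 0.05 | 0.806 | 0.822 | 0.803 |
| 25 | 0 + 0 | 0.796 | 0.798 | 0.765 |

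Under the null, in the first scenario, rejection rates were 0.030, 0.037 and 0.047. With 10 hospitals, leaving hospital out costs about 2 points (0.878 − 0.858). With 25 hospitals as fixed effects, the lost degrees of freedom cancel or exceed the gain. A random intercept and pooled sites were not simulated.

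**The case against.** For the primary outcome, the plan does commit to a model that controls for stratification, and the singular may be a slip. How hospital enters is the kind of detail that an analysis plan, not shown here, may settle. This stands: the primary finding is an ambiguity, not a shown loss.

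The error is conservative, and the sample size was calculated for an unadjusted t-test, so planned power holds without any adjustment. This stands too.

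A reader might infer more in three ways:

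- **That adjustment would lift primary power from 80.5% to some 82–86%.** That compares with a wholly unadjusted t-test, which the article does not plan for the Bayley score, and it ignores that stratified blocks already reduce the true SE. It also needs an R² that takes in fetal size and continuous gestational age, which are not stratification factors.
- **That leaving out fetal size is an error.** Size was not a stratification factor, so nothing is contradicted, even though the stratum after 36 weeks mixes two size groups.
- **That hospital differences must be large.** The article calls them slight and describes steps to limit them.

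The objection does not dispose of the secondary analyses. There the article states a method rather than omitting one, and that method ignores the factors used to randomise.

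**Conclusion.** The mismatch in the text is certain: two factors in {16a} and {16c}, one unnamed factor in {20a}, none in the secondary tests. The consequence is a possible loss of efficiency, with no bias and no excess of false positives.

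For continuous secondary outcomes, the size is as tabulated for R² of 0.05 to 0.20, and nil if the strata do not predict outcome. Dichotomous outcomes should behave in the same direction but were not calculated. For the primary outcome, the range is from nothing, if both factors are meant, to about 2 points of power if only gestational age is meant, under 10 hospitals and R² of 0.10 for each factor. Neither R² nor the number of hospitals is in the article. The planned 74 per arm and 185 in total are unaffected. This is a worthwhile, nearly free improvement rather than a threat to the trial.

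**What to change.** In {20a}, replace the singular factor with both: gestational-age stratum as a fixed effect, and hospital as a random intercept or with small sites pooled. Do not enter many small hospitals as separate fixed effects.

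Analyse the main secondary outcomes adjusted for at least the gestational-age stratum: a linear model for means, and modified Poisson or a Mantel-Haenszel relative risk for dichotomous outcomes. Keep unadjusted or exact analysis for rare events such as perinatal mortality, where models with several covariates may be unstable. For skewed outcomes the Hodges-Lehmann estimate can stay; a stratified rank test such as van Elteren's supplies a p-value but no replacement estimate.

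Adjusting for continuous gestational age and estimated fetal weight percentile at randomisation is an optional extra, not the correction of an error.

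The cost is wording, best fixed before outcome data are analysed. Both factors are already entered at randomisation, so no new data and no change in sample size are needed.
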